### Statistical Analyses

Analyses will be conducted using an intention-to-treat sample. In addition, we will conduct analyses in the per-protocol sample (ie, comprising participants who complete both baseline and postassessment measures and log into ≥4 modules of the program, defined as minimal therapeutic exposure). To assess if randomization was successful, we will compare baseline characteristics between the 3 conditions using chi-square tests (categorical) and *F* tests (continuous). Continuous outcomes will be analyzed using mixed-effects models. These analyses will model random slopes and intercepts for participants and test the fixed effects of the condition, as well as repeated assessments over time, using data from all participants. Differential intervention efficacy shows in significant interactions between the condition and time. An advantage of mixed-effects models is their ability to account for missing values through maximum likelihood estimation [116]. Significant overall effects will be followed up with contrasts comparing the 2 active conditions pooled together (ie, ICBT with and without guidance) against the control group, followed by a comparison of the 2 active conditions against each other. Significance levels will be set at P=.05. Effect sizes will be computed based on the work by Cohen [117], dividing the treatment effect by the pooled SD. In addition, we will calculate reliable changes according to the Reliable Change Index [118].

To test the mediation hypotheses, we will determine the extent of mediation of the change scores from baseline to week 5 (midassessment) and baseline to week 10 (postassessment) on the potential mechanism of change in week 10 and follow-up loneliness scores, respectively. Indirect effects will be tested by calculating bootstrapped CIs [119].

To test the moderation hypotheses, we will exploratorily include the scores of the various measures as the moderation variable to build 3-way interaction terms (condition×time×moderator) in separate mixed models. To facilitate the post hoc interpretation of interaction effects, continuous moderator variables will be grand mean centered [120]. Significant interaction effects will be followed up by applying the Johnson-Neyman technique [121].

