## Methods

### Study Design

This study uses a 3-arm RCT design to compare 2 intervention groups (SOLUS-D with individualized guidance by a coach and SOLUS-D without guidance), with a wait-list control group. Participants in the 2 active conditions will have access to the 10-week internet-based self-help intervention immediately after randomization. Participants in the wait-list control group will receive access to the program after the intervention phase of 10 weeks and the completion of the postassessment measure. Assessments for all participants will be administered at baseline (time point 0), 5 weeks (time point 1, midtreatment), and 10 weeks (time point 2, after treatment) after randomization. In addition, participants in the 2 intervention groups will be followed up at 6 (time point 3) and 12 months (time point 4) after randomization. As participants in the control group will have access to the program after 10 weeks for ethical considerations, they will not be included in the follow-up measurements. The study design is illustrated in Figure 1.

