**Secondary outcomes**							
	Depression	Patient Health Questionnaire-9	✓	✓	✓	✓	✓
	Social anxiety	Social Interaction Anxiety Scale and Social Phobia Scale	✓	✓	✓	✓	✓
	Satisfaction with life	Satisfaction with Life Scale	✓	✓	✓	✓	✓
	Social isolation	Social Network Index	✓		✓	✓	✓
	Self-compassion	Sussex Oxford Compassion Scale for the Self	✓		✓		
	Maladaptive personality traits	PID-5-BF+^c^	✓		✓		
	Misantropy	Bern Embitterment Inventory^d^	✓		✓		
	Motivation for solitude	Motivation for Solitude Scale–Short Form^d^	✓		✓		
	Negative effects	Inventory for the Assessment of Negative Effects of Psychotherapy^a^			✓		
	Patient satisfaction	Client Satisfaction Questionnaire^a^			✓	✓	
	System usability	System Usability Scale^a^			✓		
	Mental disorders	Mini Diagnostic Interview for Mental Disorders	✓			✓^a^	

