#### Primary Outcome Measure

Loneliness, assessed with the 9-item short version [66] of the Revised UCLA Loneliness Scale [67,68] at the postassessment time point, is the primary outcome. The original scale, comprising 20 items, assesses 3 different facets of loneliness: intimate loneliness, relational loneliness, and collective loneliness [69]. The short version comprises the 3 items with the highest loading on each factor [70]. The reliability and validity of this short version are comparable with those of the full 20-item version [70]. The response options are *never* (1), *rarely* (2), *sometimes* (3), and *always* (4). Ratings are summed, and scores range from 9 to 36, with higher scores indicating greater loneliness levels.

Previous studies revealed a discrepancy, for example, in the prevalence of loneliness, when assessing loneliness directly or indirectly [71]. Therefore, loneliness will be further assessed with a single direct question (“Do you feel lonely”; rated on a 4-point scale with the response options 0=*no, never;* 1=*yes, sometimes*; 2=*yes, quite often*; 3=*yes, very often*) and a 3-item very short version [72] of the UCLA Loneliness Scale for which German population norms exist [73].

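### The random-intercept-and-slope model is not identified for the four scales measured only at baseline and week 10, and the efficacy test is not tied to the week-10 primary endpoint

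*Protocol article*

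**What the plan says.** The Statistical Analyses section of the protocol article sets the model: "Continuous outcomes will be analyzed using mixed-effects models". It continues: "These analyses will model random slopes and intercepts for participants and test the fixed effects of the condition, as well as repeated assessments over time". No exception is made for outcomes with fewer occasions.

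Efficacy is read as follows: "Differential intervention efficacy shows in significant interactions between the condition and time". Then: "Significant overall effects will be followed up with contrasts comparing the 2 active conditions pooled together" against the control group, after which the two active conditions are compared with each other. Neither the interaction nor the contrasts are given a time point.

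Under Primary Outcome Measure, loneliness on the 9-item UCLA scale "at the postassessment time point, is the primary outcome". Table 2 schedules it at baseline, weeks 5 and 10, and months 6 and 12, the last two in the active arms only. Of the wait-list, Study Design says that "they will not be included in the follow-up measurements".

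Table 2 gives four secondary scales at baseline and week 10 only: the "Sussex Oxford Compassion Scale for the Self", the PID-5-BF+, the misanthropy subscale and the motivation-for-solitude subscale. The Social Network Index is scheduled at baseline, week 10, and months 6 and 12. It therefore has two occasions in the three-arm period.

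**The concern.** A random intercept and a random slope for each participant, plus a residual, need at least three occasions to be separated. Applied to a scale measured twice, the stated model has no unique solution. Software may refuse it, fail to converge, or return an arbitrary split of the variance. The analyst must then use some other model that the plan does not name.

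The second issue is the link between test and endpoint. The declared endpoint is a difference at one time point, whereas the stated test is an interaction over repeated assessments. Depending on how time is coded and which occasions enter, a significant result may or may not be a statement about week 10.

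**Working it through.** **1. Identification with two occasions.** Code baseline as 0 and week 10 as 1. Let a be the intercept variance, b the slope variance, c their covariance and e the residual variance. Then:

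- Var(baseline) = a + e
- Cov(baseline, week 10) = a + c
- Var(week 10) = a + 2c + b + e

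That is 3 equations for 4 unknowns. Replacing (a, b, c, e) by (a − k, b − 2k, c + k, e + k) leaves all three unchanged, so the data cannot choose between them. The matrix of derivatives has rank 3 for 4 parameters. With weeks 0, 5 and 10 there are 6 distinct variances and covariances and the rank is 4, so for loneliness a random intercept and linear slope are identified.

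**2. What is lost.** In one simulated two-occasion data set (100 per arm, correlation 0.60), fixing the residual variance at 0.05, 0.15 or 0.30 gave slope variances of 0.553, 0.353 and 0.053. The log-likelihood was the same each time (−480.994). So were the condition-by-time estimate (−0.217) and its standard error (0.114), and the estimate equals the difference in mean change. Only the variance split is undetermined.

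**3. Interaction against the week-10 endpoint.** Three readings are open.

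- *Linear time, weeks 0, 5, 10.* The within-person slope weights are (t − 5)/50, that is (−1, 0, +1)/10. In complete data, slope × 10 is exactly the change from baseline to week 10, whatever happens at week 5. With 25% missing at week 10 only, the ratio to the true week-10 difference is 0.92 if the whole effect comes after week 5 and 1.08 if it is all there by week 5. It is 0.96 or 1.04 if 25% or 75% of the effect is there by week 5. These ratios assume intercept variance 0.6, slope variance 0.001 per week squared, zero covariance and residual variance 0.3.
- *Categorical time, weeks 0, 5, 10, three arms.* The overall interaction has (3 − 1)(3 − 1) = 4 degrees of freedom and tests weeks 5 and 10 jointly. A difference at week 5 alone can make it significant.
- *All five occasions in one model.* The wait-list contributes nothing after week 10, and the interaction covers up to 12 months in the active arms.

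Only the first reading matches the endpoint, and the text does not select it.

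**4. The plan's own sample size.** Inputs from Sample Size: f = 0.10, r = 0.60, α = .05, two active arms. With m = 2 occasions, λ = f²·N·m/(1 − r). For N = 160 this is 0.01 × 160 × 2/0.40 = 8.0, and the F test with 1 and 158 degrees of freedom has power 0.803. The stated 80 per arm is reproduced.

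The implied effect follows, with outcome SD 1. The change score has variance 2(1 − 0.60) = 0.80. Setting δ²/(2 × 0.80/80) = 8.0 gives δ² = 0.16, so δ = 0.40 SD as a difference in change.

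**5. Gain from baseline adjustment.** Take 100 randomized per active arm and 25% dropout, so 75 completers.

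| Analysis | Error variance | λ | Power |
|---|---|---|---|
| Difference in change | 0.80 | 0.16/(2 × 0.80/75) = 7.5 | 0.777 |
| Baseline-adjusted week 10 | 1 − 0.60² = 0.64 | 0.16/(2 × 0.64/75) = 9.375 | 0.860 |

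**The case against.** The strongest reply has three parts.

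- *The unidentified model does little harm.* The treatment estimate and its standard error are the same however the variance is split, and dropping the random slope is forced by the schedule rather than chosen from results. This largely stands. It limits the consequence, but the stated model still cannot be fitted for these outcomes.
- *Time coding, occasions and the contrast time point are details for an analysis plan that is not shown.* This stands for the missing detail taken alone. The first defect is different: it is a conflict between a stated model and a stated schedule.
- *The context points to weeks 0 to 10.* The Abstract separates the posttreatment primary outcome from maintenance at 6 and 12 months, the wait-list has no follow-up, and the sample size reproduces with two occasions (three would give 65 per arm). This also stands.

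A reader might go further and infer that the primary test uses a straight line through month 12, which would greatly understate an effect reached by week 10 and then held, or more generally that the slope fails to estimate the week-10 difference. The document supports neither. It nowhere says that fixed time is linear or that the follow-ups enter the same line, and over weeks 0, 5 and 10 a linear slope reproduces the week-10 change exactly in complete data.

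**Conclusion.** The model as written is not identified for four secondary scales, nor for the Social Network Index if only the three-arm period is modelled. This rests on counting parameters and needs no assumption about the data. Treatment effects on those outcomes remain estimable, and the primary outcome is not touched by this defect.

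The primary test is not tied to week 10. It agrees with the endpoint under one plausible reading and need not under others, such as the joint test of weeks 5 and 10. That is a looseness to close, not evidence that the primary analysis is wrong.

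The gain from the recommended analysis, from about 0.78 to about 0.86 power for guided versus unguided, rests on the protocol's r = 0.60 and f = 0.10 (0.40 SD difference in change), equal variances, and 75 completers per arm. Overall this is worth correcting before analysis and does not threaten the trial.

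**What to change.** - *Scales with only baseline and week 10 in the three-arm comparison* (the four scales and the Social Network Index): drop the random slope and use a baseline-adjusted week-10 comparison. A two-occasion model with unstructured covariance and a common baseline mean does the same and keeps participants who lack the week-10 value.
- *Primary outcome:* model baseline, week 5 and week 10 with time categorical and an unstructured covariance instead of random slopes. Name the baseline-adjusted week-10 contrast as the primary test, for pooled active versus wait-list and for guided versus unguided.
- *Maintenance:* analyse months 6 and 12 in a separate model of the two active arms.

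The cost is a change of wording, to be dated before the outcome data are analysed. For loneliness the unstructured covariance over three occasions has 6 parameters instead of 4. No extra participants or assessments are needed.

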**Methods:**

A total of 250 participants will be randomly assigned to 1 of 2 intervention groups (SOLUS-D with guidance or SOLUS-D without guidance) or a wait-list control group (2:2:1 allocation ratio). Adult participants experiencing high levels of loneliness will be recruited from the general population. Individuals currently experiencing at least moderately severe depressive symptoms, an ongoing severe substance use disorder, previous or current bipolar or psychotic disorder, or acute suicidality will be excluded from the trial. Assessments will take place at baseline, 5 weeks (midassessment), and 10 weeks (postassessment). The primary outcome is loneliness assessed using the 9-item University of California, Los Angeles Loneliness Scale at the posttreatment time point. Secondary outcomes include depressive symptoms, symptoms of social anxiety, satisfaction with life, social network size, and variables assessing cognitive bias and social behavior. The maintenance of potentially achieved gains will be assessed and compared at 6 and 12 months after randomization in the 2 active conditions. Potential moderators and mediators will be tested exploratorily. Data will be analyzed on an intention-to-treat basis.

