**Primary outcome**							
	Loneliness	UCLA^b^ Loneliness Scale 9-item version	✓	✓	✓	✓	✓

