### Sample Size

A power analysis was conducted using G*Power 3 [114]. We aim to detect small effect sizes [115] of 𝑓=0.10 (equivalent to Cohen *d*=0.20) regarding the time×group interaction for the 2 active conditions at an α error level of .05. A power analysis revealed that a sample size of 80 participants in each of the active study arms is required to detect a statistically significant difference with a power (1 – β) of 0.80, assuming correlations of *r*=0.60 between before and posttreatment measures, as previously found in another trial on ICBT for loneliness [57]. Sample size was further estimated based on a dropout rate of approximately 25%. We finally decided to randomize 100 participants to each of the active conditions. For the comparisons between the active conditions and the wait-list, 50 participants were considered sufficient for the wait-list control group condition as between-group effect sizes were assumed to be large based on the results of the aforementioned Swedish trials [54,57]. Consequently, we aim to randomize 250 participants with a randomization ratio of 2:2:1.

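### The condition-by-time test leaves baseline means free by arm and so gives up about 20% of the effective sample size (at r = 0.60, equal SDs) compared with adjusting for baseline loneliness

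*Protocol article*

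**What the plan says.** The primary endpoint is a score at one time: "The primary outcome is loneliness assessed using the 9-item University of California, Los Angeles Loneliness Scale at the posttreatment time point". Table 2 shows that the same scale is also collected at baseline and at 5 weeks from all three arms.

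The Statistical Analyses section describes the model: "These analyses will model random slopes and intercepts for participants and test the fixed effects of the condition, as well as repeated assessments over time". It then names the efficacy test: "Differential intervention efficacy shows in significant interactions between the condition and time". It mentions no baseline covariate and no constraint of equal baseline means.

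The Sample Size section powers the same term for guided versus unguided treatment. It takes f = 0.10, glossed as "equivalent to Cohen *d*=0.20) regarding the time×group interaction for the 2 active conditions at an α error level of .05", with r = 0.60 as the correlation "between before and posttreatment measures, as previously found in another trial on ICBT for loneliness". The result is 80 per active arm. Allowing for about 25% dropout, 100 are randomised to each active arm.

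On baseline comparability, the Statistical Analyses section says: "To assess if randomization was successful, we will compare baseline characteristics between the 3 conditions", using chi-square and F tests.

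**The concern.** With condition, time and their interaction all in the model, each arm has its own estimated baseline mean. The interaction at 10 weeks is then the between-arm difference at week 10 minus the between-arm difference at baseline. Under randomisation the true baseline difference is zero, so subtracting an estimate of it adds noise. If the arms differ at baseline by chance, a change score also over-corrects, because with r below 1 only part of that difference is expected to persist to week 10.

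Baseline adjustment, or a model with a common baseline mean, avoids this at no cost in data. The gain matters most for guided versus unguided, the comparison that determined the size of the active arms and where the protocol expects a small effect. The same gain is available for every continuous outcome measured at baseline.

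**Working it through.** **Inputs.** From the Sample Size section: f = 0.10, alpha = 0.05, power 0.80, r = 0.60, 80 per active arm, 100 randomised per active arm, about 25% dropout. Assumption: equal SDs at baseline and week 10, relaxed in step 4, since the article gives no SDs.

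**1. Reproduce the stated sample size.** For a two-group, two-occasion interaction the noncentrality is f² × N × m / (1 − r) = 0.01 × 160 × 2 / 0.40 = 8.0. With N = 160 (80 per arm) this gives power 0.803, so the stated figure reproduces. A three-occasion version gives N = 130 and does not match.

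**2. Express that as a difference in change.** In units of the single-occasion SD, a change score has variance 2(1 − r) = 0.80. The same noncentrality from a two-sample comparison is δ² / (2 × 0.80 / 80) = δ² / 0.02. Setting this to 8.0 gives δ = 0.40. The 80 per arm therefore corresponds to a 0.40 SD difference in change. The normal approximation gives 79 per arm.

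**3. Compare the two analyses at r = 0.60.**
- Difference in change: 2(1 − r) = 0.80
- Baseline-adjusted: 1 − r² = 1 − 0.36 = 0.64
- Loss of effective sample size: 1 − 0.64/0.80 = 20%
- Extra participants needed to match adjustment: 0.80/0.64 = 1.25, that is 25% more

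With all three assessments (0, 5 and 10 weeks), comparing free with constrained baseline means, the loss is 20% with categorical time. It is 20% to 21% with linear time, taking the correlations with week 5 as 0.60 to 0.77.

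**4. Vary the assumptions.** Let k be baseline SD divided by week-10 SD. The change variance is 1 + k² − 2rk in week-10 units; the adjusted variance stays at 0.64.

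| k | Change variance | Loss |
|---|---|---|
| 0.8 | 1 + 0.64 − 0.96 = 0.68 | 6% |
| 0.9 | 1 + 0.81 − 1.08 = 0.73 | 12% |
| 1.0 | 0.80 | 20% |
| 1.1 | 1 + 1.21 − 1.32 = 0.89 | 28% |

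With equal SDs the loss is (1 − r)/2: 25% at r = 0.5, 20% at 0.6, 15% at 0.7.

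**5. Power for guided versus unguided.** With 25% dropout, 100 × 0.75 = 75 completers per arm (completers only, equal SDs, normal approximation).

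| True difference | SE, change: √(0.80 × 2/75) = 0.146 | SE, adjusted: √(0.64 × 2/75) = 0.131 |
|---|---|---|
| 0.40 SD | power 0.78 | power 0.86 |
| 0.20 SD | power 0.28 | power 0.33 |

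For 80% power, the required number per arm falls from 79 to 63 at 0.40 SD, and from 314 to 252 at 0.20 SD.

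**The case against.** The strongest reply is that nothing here is an error. A condition-by-time interaction is unbiased under randomisation, and the trial was sized for exactly this term at r = 0.60, so its nominal power already reflects the less efficient test. That stands: the point is avoidable imprecision.

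The reply can also press on size. The 20% needs equal SDs, and entry requires a UCLA-9 score of at least 18 (Inclusion and Exclusion Criteria), which may narrow the baseline distribution. At k = 0.8 the loss is only 6%. That stands too, and is why a range is given. With r = 0.60 the change variance is not below 0.64 at any k, so in large samples adjustment does not lose precision.

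An unseen analysis plan may add covariates. It may, but the article positively states the test and the condition effect, so this is a comment on a stated choice.

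Several stronger readings are tempting but not supported:
- A reader might take the 25% as the share of the sample lost. It is the number of extra participants needed; the loss at r = 0.60 is 20%.
- A reader might infer that baseline loneliness goes unused apart from the significance tests. It is the first of the repeated measures in the model.
- A reader might read the power gain of 0.78 to 0.86 as applying to the stated d = 0.20. It applies to 0.40 SD; at 0.20 SD power stays low either way.
- A reader might conclude that the baseline tests will usually declare a sound randomisation failed. With 20 to 25 independent tests at 0.05 the chance of at least one false flag would be 64% to 72% (1 − 0.95²⁰, 1 − 0.95²⁵). But these scales are likely to be correlated, the article does not say which characteristics are tested, and no decision depends on the result.

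**Conclusion.** The point holds as a missed gain in precision. The planned test is valid and consistent with the sample size calculation, but it is a difference in change and is less precise than an analysis adjusted for a baseline score already collected. The best single figure is a 20% loss of effective sample size, resting on the protocol's r = 0.60 and on equal SDs; a plausible range is 6% to 28% for SD ratios of 0.8 to 1.1. For guided versus unguided with 75 completers per arm and equal SDs, that decides whether power is just below or comfortably above the planned 0.80 at the 0.40 SD effect implied by the calculation.

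The baseline tests are a secondary matter. Allocation is automated, so chance accounts for baseline differences, and a significance test cannot show whether randomisation was successful. The tests affect neither the estimate nor the power.

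**What to change.** Estimate the week-10 contrasts for the primary and other continuous outcomes from a mixed model in which the three arms share one baseline mean: keep time and condition-by-time terms, with no condition effect at time 0. This keeps everyone with any assessment in the intention-to-treat analysis. The alternative is to use the baseline score as a covariate for the later scores. It gives the same precision in the two-occasion calculation, but participants with baseline data only contribute no outcome, which matters with about 25% dropout expected.

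Replace the chi-square and F tests of baseline characteristics with a descriptive table by arm.

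The cost is a change of model specification and no new data. Because 134 participants had been randomised when the article was submitted, the change should be documented and dated before outcome data are analysed.

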### Objectives

Given the need for more high-quality RCTs of interventions for alleviating loneliness, this study will be conducted to investigate the following objectives. First, we will test the efficacy of 2 web-based interventions (ICBT with or without guidance) compared with a wait-list control group regarding loneliness (primary outcome) and a range of secondary outcomes (eg, depression, anxiety, satisfaction with life, and factors of the cognitive model of loneliness). We expect individuals in both intervention groups to show a greater reduction in loneliness and more pronounced effects in the secondary outcomes than in the wait-list control group.

Second, we will compare the efficacy and long-term effects of the 2 active interventions regarding primary and secondary outcomes to specify the effects of added human contact through guidance. We expect greater changes in the primary and secondary outcomes in the intervention with guidance than in the intervention without guidance.

Third, we will test potential baseline predictors for the efficacy of the interventions and explore moderators between the 2 active conditions to better understand which intervention (with or without guidance) works best for whom. Considering the exploratory nature of this objective, we have no specified hypothesis for this objective.

Finally, we will explore potential mediators (mechanisms of change) of the interventions. We expect changes in cognitive bias and counterproductive social behavior, as described in the cognitive model of chronic loneliness [19], to explain reductions in loneliness.

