## Discussion

### General Discussion

Chronic loneliness is a prevalent clinical phenomenon in the population, with a variety of adverse effects on mental and physical health [8], leading to increased mortality [9]. Psychological interventions have generally been shown to be effective in reducing loneliness [48]. Such interventions at an individual level may play a crucial role in reducing the burden of loneliness and complementing social and societal-based interventions [122-124]. Although various treatments for alleviating loneliness have been developed and tested, more well-controlled clinical trials are needed to inform about efficacious interventions for loneliness.

This study aims to test the efficacy of an internet-based self-help intervention (*SOLUS-D*) in reducing loneliness. We expect participants in both intervention groups to show greater decreases in loneliness compared with a wait-list control group at the posttreatment time point. Furthermore, reductions in loneliness will be expected to be more pronounced in participants receiving guidance than in the group without guidance. By comparing the 2 intervention groups with and without guidance, we will be able to inform about the incremental effect of guidance beyond that of the ICBT intervention. We will also look at acceptability aspects such as intervention satisfaction, adherence, and potential negative effects to further refine the intervention. In addition, we will investigate potential moderating variables on an exploratory level to gain insights into how and for whom exactly the intervention works. Furthermore, knowledge on mechanisms of change in treating chronic loneliness will be expanded. This will provide further insight into the maintaining factors of chronic loneliness that interventions should focus on and, at the same time, test the proposed model of chronic loneliness [19]. Finally, the results of this study will inform which individuals can profit (most) from an internet-based ICBT intervention for loneliness.

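### The hypothesis is that both interventions beat the wait-list, but the only named contrast with the wait-list pools the two active arms, so neither arm is tested on its own

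*Protocol article*

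**What the plan says.** The first objective is worded for two interventions: "we will test the efficacy of 2 web-based interventions (ICBT with or without guidance) compared with a wait-list control group" (Protocol article, Objectives). The hypothesis follows: "We expect individuals in both intervention groups to show a greater reduction in loneliness". The General Discussion repeats it for the posttreatment time point: "We expect participants in both intervention groups to show greater decreases in loneliness compared with a wait-list control group".

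The Statistical Analyses section then sets out the tests. Continuous outcomes go into a mixed model, and "Differential intervention efficacy shows in significant interactions between the condition and time". If the overall effect is significant, two contrasts are planned. The first is given as "contrasts comparing the 2 active conditions pooled together (ie, ICBT with and without guidance) against the control group". The second sets guided against unguided, in the words "followed by a comparison of the 2 active conditions against each other". On the error level it says "Significance levels will be set at P=.05". No contrast of the guided arm alone, or of the unguided arm alone, with the wait-list appears anywhere in the article.

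**The concern.** The hypothesis concerns two differences, guided minus wait-list and unguided minus wait-list. The three-condition overall test does not say which arm differs. The pooled contrast is therefore the only directed test against the wait-list, and it tests the mean of those two differences. A mean can be clearly above zero when one component is small or absent.

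The article itself gives reasons to expect the arms to differ. It predicts a larger change with guidance. It also says that earlier ICBT designs for loneliness could not separate human contact from the program (Internet-Based Interventions for Loneliness). The pilot effect that it cites, d=0.77, is for a guided program, and it quotes no effect of an unguided program against a wait-list. At stake is whether the trial can support its first objective, on the primary outcome, for each version of the program.

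This is not a matter of an article leaving detail to a fuller plan. The contrasts are named, and the named set omits the two that the hypothesis needs.

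**Working it through.** **The plan's own figure.** The Sample Size section powers guided against unguided for "small effect sizes [115] of 𝑓=0.10", r=0.60, alpha .05 and power .80, and gives 80 per active arm. With the repeated-measures interaction formula for two groups and m=2 measurements, λ = f²·N·m/(1−r) = 0.01 × 160 × 2/0.40 = 8.0, and the noncentral F power on 1 and 158 df is 0.803. The figure reproduces. No power figure is given for the comparison with the wait-list.

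**Inputs.** From the article: 100/100/50 randomised, dropout about 25%, r=0.60, and earlier effects against a wait-list of d=0.77 and d=0.71. Assumed: two-sided tests, equal SDs, the same dropout in every arm (75/75/38 analysed), one pre-post comparison in place of the full mixed model, and the unguided effects, because the article gives none. The change-score SD in posttest SD units is √(2(1−0.60)) = 0.894.

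**Standard errors.**
- Pooled arms versus wait-list: 0.894 × √(1/150 + 1/38) = 0.162
- One arm versus wait-list: 0.894 × √(1/75 + 1/38) = 0.178
- Guided versus unguided: 0.894 × √(2/75) = 0.146

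**Case A: guided 0.77, unguided 0.** The pooled effect is (0.77 + 0)/2 = 0.385, and 0.385/0.162 = 2.37, which gives roughly 66% power. In 400,000 simulated trials the overall test and the pooled contrast were both significant in 65%. A separate unguided contrast favoured the program in 2.5%. Guided versus unguided has 0.77/0.146 = 5.27 and was significant in more than 99.9%.

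**Case B: guided 0.71, unguided 0.30.** The pooled effect is 0.505, and the overall test and pooled contrast succeed in 87%. For the unguided arm alone, 0.30/0.178 = 1.68, which gives 39% power. Both separate contrasts succeed in 39%. In 48% of trials the pooled result is positive while unguided versus wait-list is not significant. The unguided effect is real here, so these are not false claims. They show that the pooled contrast answers an easier question than the one the hypothesis asks.

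**Sensitivity.** The range below covers SD 1 (posttest only) to SD 0.8 (baseline-adjusted), each at 75% retention and at full numbers.

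| | Overall and pooled | Both arms separately |
|---|---|---|
| Case A | 56% to 86% | 2.5% |
| Case B | 78% to 98% | 32% to 58% |

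**Feasibility of separate contrasts (SD 0.894, 75/75/38).** At d=0.71 in each arm, 0.71/0.178 = 3.99, so power is about 98% per arm and 96% for both. At full numbers it is over 99% for both. With SD 1 and 75% retention it is 94% per arm and 91% for both. If each arm has only d=0.50, power is 80% per arm and about 70% for both, against about 78% for the overall test plus the pooled contrast.

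**The case against.** The pooled contrast and the guided-unguided contrast are a recognised orthogonal pair that uses both condition degrees of freedom. Each arm's difference from the wait-list can also be recovered from the same model, as the pooled difference plus or minus half the guided-unguided difference. This stands: neither data nor model is lacking. What is lacking is a named test for each arm and a rule for what it would establish.

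A reader might infer that pooling would hide an unguided arm with no effect, because the guided-unguided contrast is too weak to show it. The figures do not support that. In Case A that contrast is significant in more than 99% of trials. With the unguided effect at zero and guided effects from 0.2 to 0.77, a positive pooled contrast with no significant arm difference occurs in at most about 5% of trials. Low power matters when the arms differ little. At assumed effects of 0.50 and 0.30, the arm contrast has about 28% power, and 43% of trials show a positive pooled result with no significant arm difference. That pattern invites the reading that both programs work without testing it.

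A reader might also argue that pairwise tests at .05 after a significant overall test already control the error rate with three groups. That requires the overall test and the pairwise tests to address the same null hypothesis. Here the overall test is condition by time over baseline, 5 and 10 weeks, and the article does not say how time is coded. With categorical time, a difference at week 5 alone can make it significant. In a simulation of that situation (week-5 effect d=0.77, correlation 0.5 between the change scores, both assumed), at least one of three week-10 pairwise tests was falsely significant in 12% of trials.

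**Conclusion.** The mismatch is real. Followed as written, the plan tests the average of the two programs against the wait-list and the difference between them, but not the stated hypothesis that each program beats the wait-list. The two contrasts together leave the unguided arm undecided, because a positive pooled result with guided ahead of unguided fits an unguided effect of zero as well as one above zero.

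The size depends on unguided effects that the article does not give. Under the assumptions above, the pooled route succeeds in about 65% of trials when only the guided arm works, and in about 87% when the effects are 0.71 and 0.30, where both separate contrasts succeed in about 39%. These are illustrations, not forecasts. The article does not say that the unguided program is ineffective, and it reports that loneliness declined in an earlier unguided program. The conclusion that the named tests do not match the hypothesis does not rest on these figures.

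**What to change.** In Statistical Analyses, name guided versus wait-list and unguided versus wait-list at week 10 as the confirmatory contrasts for the primary outcome. Test each at two-sided .05, and require both to be significant before claiming that both interventions are efficacious. That claim needs no split of alpha, because it is made only when both tests succeed. If a claim for one arm alone is wanted, state a fixed testing order or a Holm correction, rather than relying on the overall condition-by-time test. Then test guided versus unguided, and keep the pooled contrast as supportive.

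The change takes a sentence or two and no extra participants. The cost is precision: each contrast uses 100 rather than 200 randomised active participants, so the standard error rises from 0.162 to 0.178 after dropout. At d=0.71 per arm this leaves about 96% power for both, and at d=0.50 about 70%. Because 134 participants had been randomised when the article was submitted, the change should be recorded before outcomes are examined by arm.
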